#### Integration of collected data with Alzheimer Evaluation Units (AEUs)

The information collected through the questionnaire will be integrated with information already held by the AEUs. The following scales will be obtained for each patient: MMSE, Clinical Dementia Rating (CDR) and Neuropsychiatric Inventory (NPI). Information concerning hospitalizations and episodes of institutionalization in other residential care facilities will also be retrieved from regional hospital discharge and residential care databases.

#### Statistics

The first step of the analysis will be exploratory in nature. A descriptive analysis of the sample will be conducted using uni- and bi-variate statistical analyses, with the aim of verifying the comparability of the three study groups. Significant differences between exposures and outcomes will be compared using the chi-square test, Fisher’s exact test (in the case of categorical variables), t-test or analysis of variance (ANOVA) test (for comparisons of continuous variables between groups according to a normal or non-normal distribution). Additionally, to check possible selection bias, the characteristics of the subjects in the sample will be compared to those of non-respondents for available variables (for example age, gender, place of living and MMSE score).

The primary outcome, caregiver burden inventory, will be compared between the three groups using analysis of covariance (ANCOVA). The analyses will adjust for variables which are non-homogenously distributed in the three groups and control for other factors that the literature suggests are associated with the two outcomes (for example gender and age of caregivers, severity of dementia, and use of private care workers) [46,47].

The primary outcome, number of days spent at home by the AD patient during the observation period, will be similarly analyzed using ANCOVA. The events of hospitalizations and institutionalization will also be analyzed with the following: the distribution of events and event-free survival (days spent at home) will be described for the entire sample using Kaplan-Meier estimator modeling; Mantel-Cox log-rank test or generalized Gehan-Breslow-Wilcoxon test will be used to evaluate bivariate differences in survival distribution between identified subgroups; Cox proportional hazard modeling will be used to analyze the multivariate effects of identified risk factors and other determinants on time spent at home under the proportional hazards assumption; and adjusted hazards ratio (HR) and 95% confidence intervals (CI) will be calculated to test the direction and strength of the influence of individual factors on event-risk and event-free survival. The analyses of outcomes will be intention-to-treat (ITT).

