#### Randomization, allocation and blinding

A letter with an invitation to participate in the project will be sent to a list of potential participants, randomly extracted from the AEU registers. A total of 640 invitations will be sent, considering a response rate of 70% (a reasonably high rate, since the project has been endorsed by the Italian regional health system and several local patients' organizations). Families agreeing to be contacted will receive a home visit by a nurse. Both caregivers and patients will be requested to sign a full informed consent to participate in the study. The nurses who will make the home visits and administer the questionnaires will be blinded at their first visit.

The allocation sequence will be generated using the statistical software STATA (College Station, TX, USA). Dyads in blocks of 15 and consequently enrolled will be sent by a nurse coordinator in the five health districts directly to the project manager (CC). In each block, five dyads will be allocated to each arm. The randomization will be performed by the project manager, who will not conduct any assessment related to treatment outcomes or have any contact with line staff involved in the intervention, in order to preserve allocation concealment and prevent selection bias (Figure 1).

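### The t-test and ANOVA are assigned by distribution rather than by number of groups, and observed imbalance between arms is used to choose covariates for both primary ANCOVAs

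*Protocol article*

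**What the plan says.** All the relevant text is in the Statistics section of the protocol article.

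- The first step is descriptive and bivariate, "with the aim of verifying the comparability of the three study groups".
- The tests are introduced with "Significant differences between exposures and outcomes will be compared using the chi-square test". Fisher's exact test is also named for categorical variables. Continuous variables get a "t-test or analysis of variance (ANOVA) test (for comparisons of continuous variables between groups according to a normal or non-normal distribution".
- The Caregiver Burden Inventory (CBI) "will be compared between the three groups using analysis of covariance (ANCOVA"). On covariates: "The analyses will adjust for variables which are non-homogenously distributed in the three groups". The analyses will also "control for other factors that the literature suggests are associated with the two outcomes", with caregiver gender and age, severity of dementia and use of private care workers given as examples.
- Days at home, the other primary outcome, "will be similarly analyzed using ANCOVA".

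There are three arms in equal ratio. The section on randomization, allocation and blinding says: "In each block, five dyads will be allocated to each arm".

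**The concern.** There are two separate problems.

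**The test rule.** The sentence makes the choice between t-test and ANOVA depend on whether the variable is normally distributed. What separates the two tests is the number of groups. Followed literally, a skewed variable goes to ANOVA as though ANOVA were the remedy for skewness, and a normal variable goes to a t-test, which cannot compare three arms at once. Skewed variables are likely: the questionnaire collects hospitalizations, weekly hours of paid care and weekly hours of work lost.

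**The covariate rule.** Adjusting for whatever turns out to be unevenly distributed makes the primary model depend on the data. Under randomization any imbalance in a true baseline variable is due to chance, and its observed size is a poor guide to whether the variable predicts the outcome. At stake is how far the two primary models are fixed before the data are seen.

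**Working it through.** The plan states no figure on this point, so there is none to reproduce. The checks below use three arms of 150 (from the protocol article). The 5% level for comparability tests is an assumption, because the Statistics section gives none.

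**1. Are the t-test and ANOVA alternatives for different distributions?** For two groups, F = t². On two simulated samples of 150 from an exponential (clearly non-normal) distribution, t² = 1.2787 and F = 1.2787, with p = 0.2591 for both. They are the same test when there are two groups, so distribution cannot be the basis for choosing between them.

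**2. Does ANOVA break down on skewed data at this size?** With lognormal data (sigma 1.2), no true difference and 5,000 runs, ANOVA rejected in 4.2% of runs, close to the nominal 5%. With one arm multiplied by 1.4, ANOVA detected the difference in 42% of runs and Kruskal-Wallis in 69%. The cost is lost sensitivity, not false positives. The shape and the shift are illustrative assumptions.

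**3. Does the comparability step feed the primary models?** Setting the sentences side by side:

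- The aim of the first step is to check whether the three groups are comparable.
- The next paragraph adjusts for variables that are not homogeneous across the three groups.
- No other check of homogeneity is described, and no p-value or other threshold is given.
- Days at home is analysed in a similar way, and the covariate sentence speaks of both outcomes.

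The link is therefore an inference, though the natural one. It covers only the data-driven part of the covariate set.

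**4. How many covariates would enter by chance?** With one correct three-group test per variable at level 0.05 and k independent balanced variables, the expected number is 0.05 × k and the chance of at least one is 1 − 0.95^k. The plan gives no k, so a range is shown.

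| k (assumed) | Expected number entering by chance | Chance of at least one |
|---|---|---|
| 10 | 0.5 | 40% |
| 20 | 1.0 | 64% |
| 50 | 2.5 | 92% |

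A simulation of 20,000 runs with normal data gave a 4.8% flag rate per variable for one ANOVA, consistent with the 0.05 used here. With a covariate list fixed in advance, the number entering by chance is 0.

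**The case against.** The strongest reply is that the parenthesis is loose wording in a step the plan itself calls exploratory. On this view the test sentence speaks of exposures and outcomes rather than baseline variables by arm, and nothing says that a p-value decides covariate entry. The primary outcomes have their own analyses, and adjusting a randomized comparison for a variable with a chance imbalance does not grossly bias it.

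Much of this stands. The link to covariate entry is inferred, the literature-based factors enter whatever the tests show, and the harm to the estimates is small. It does not rescue the test rule: condensing a protocol into an article explains missing detail, not a wrong pairing. Nor does it answer the covariate rule, which is stated outright for the primary analysis.

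A reader might infer that the wrong pairing itself decides the primary covariates, and that three pairwise t-tests per variable would raise the chance flag rate to about 12% (12.4% in simulation), or about 2.4 variables in 20 (20 × 0.12) instead of 1. The document does not support this:

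- It does not say that pairwise tests would be run uncorrected, or that any one of them would flag a variable.
- The section on multiple comparisons names Bonferroni for fewer than 10 comparisons. Its reach to baseline checks is unclear, but with it the rate is 4.4%.
- The count of 20 is assumed and treats every variable as continuous, whereas categorical variables have their own tests.
- Data-driven entry would remain if every test were chosen correctly, so the pairing does not cause it.

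**Conclusion.** The point holds as two minor but real defects.

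- The rule for continuous variables is wrong as written, and no test suited to skewed data is named. On skewed variables the practical loss is sensitivity; the error rate of ANOVA stays near nominal at 150 per arm.
- Both primary ANCOVAs take part of their covariate set from observed imbalance, with no criterion given. At an assumed 5% level, about 1 in 20 balanced variables would enter by chance.

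This rests on reading the comparability step as the source of the data-driven covariates, and on an assumed test level and number of variables. It does not show that either primary estimate would be materially biased. The loss is in pre-specification.

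**What to change.** 1. For description only, compare the three arms by ANOVA (approximately normal) or Kruskal-Wallis (skewed). Compare two groups, such as respondents and non-respondents, by t-test or Mann-Whitney.
2. Delete observed imbalance as a reason for entering a covariate. Fix the ANCOVA covariates in advance: baseline CBI (for the CBI model), health district, caregiver age and sex, dementia severity, and baseline use of private care workers.

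Both changes are needed, because correcting the test names alone would leave covariate entry dependent on the data. The cost is a short edit to the Statistics section; baseline CBI, district, caregiver age and sex, dementia severity and paid care are already within the planned data collection. The downside is that the primary models will not adjust for chance imbalances outside the list. These can be examined in a sensitivity analysis labelled as such.

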#### Outcomes of the study

The main outcomes of the study are: 1) caregiver burden, measured using the Caregiver Burden Inventory (CBI) multi-dimensional questionnaire, administered by a trained nurse. The CBI has five subscales: time-dependence burden, developmental burden, physical burden, social burden and emotional burden, and includes a set of 24 items evaluated using a 5-point Likert scale ranging from 0 (not at all) to 4 (very much), which are summed. A total score higher than 36 indicates a risk of stress, whereas scores near or slightly above 24 indicate a need to seek some form of respite care [36]. During the study, the Italian version of the CBI validated by Marvardi and colleagues will be used [37]; and 2) the actual number of days spent at home by the AD patient during the observation period, defined as days free from episodes of institutionalizations, inpatient hospitalizations and brief stays in an observation unit of an emergency room. This outcome will be treated as a continuous variable and will be calculated at each assessment (6 months, M6; 12 months, M12; and 24 months, M24) by subtracting from the total days of observation, the number of days of institutionalization in an assisted residence facility, care home and/or nursing home inpatient, hospitalizations, and brief stays in an observation unit of an emergency room.

In addition, the following outcomes will be evaluated at the end of the trial: 1) quality of life of the caregiver of the AD patient, measured using the Italian validated version of the quality of life questionnaire, SF-12 [38,39]; 2) anxiety and depression of caregivers, measured using the Italian validated version of the Hospital Anxiety and Depression Scale (HADS) [40,41]. HADS is a 14-item scale, seven of the items relate to anxiety and seven relate to depression, each item is a Likert scale scoring from 0 to 3, and this means that the overall score for either anxiety or depression will be between 0 and 21; and 3) abuse and mistreatment risk of AD patients, using the CASE instrument, an 8-item screening tool designed to assess caregivers for potential abuse. Answers are either given as ‘yes’ or ‘no’, and an answer of ‘yes’ for a question equals one point. A score of four or more is considered ‘abuse likely’, but a score of one can also mean that abuse is likely, depending on the question [42]. An Italian validation of this instrument is planned in a separate study at the end of the trial.

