#### Sample size calculation

An estimation of the sample size was carried out by considering the two main outcomes separately.

The first principal outcome is caregiver burden. A previous Italian study estimated that the level of burden of AD patients' caregivers, as measured by the CBI [36], was equal to 32.5, with a standard deviation (SD) equal to 18 [37]. The planned sample size of 150 caregivers is sufficient to detect an effect that lowers the CBI score to 24, with a SD equal to 12 in the treatment group and a null effect in the control group. The statistical power was fixed at 80%, with a 0.05 significance level and a drop-out rate equal to 15%. A CBI score of 24 coincides with a ‘sentinel’ level beyond which it is suggested that caregivers need to receive additional support from the health care and social services.

The second principal outcome is actual days spent at home by the AD patient in the past year. The hypothesis that this outcome is the same in the treated and the untreated populations will be tested. The calculation was made considering a type 1 error (α error) of 0.05, using a one-tailed t-test and assuming a 10% difference between values. Regarding this as the smallest effect of clinical relevance, a sample of 150 patients per treatment group, with a drop-out rate equal to 15%, will be adequate to achieve an 80% probability of rejecting the null hypothesis.

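### The three-arm ANCOVA, in its ordinary form, applies one residual variance to every pairwise contrast, although both primary outcomes can be expected to vary less in an arm that works

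*Protocol article*

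**What the plan says.** **Model.** The Statistics section compares CBI across the three groups in an analysis of covariance and states that the "number of days spent at home by the AD patient during the observation period, will be similarly analyzed using ANCOVA". Adjustment is for unbalanced variables and known prognostic factors. No unequal-variance or robust method is named, and the article does not say how pairwise contrasts are formed.

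**Days at home.** Under Outcomes of the study: "This outcome will be treated as a continuous variable". It is calculated "by subtracting from the total days of observation, the number of days of institutionalization in an assisted residence facility" and other days away, so it cannot exceed the observation time. The sample size section tests it "using a one-tailed t-test and assuming a 10% difference between values". It gives neither a mean nor an SD.

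**CBI.** The sample size section takes a mean of 32.5 and SD of 18 from an earlier Italian study, and plans for a fall to 24 "with a SD equal to 12 in the treatment group".

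**Multiplicity.** The section on multiple comparison issues plans a Bonferroni correction for fewer than 10 comparisons, but introduces it for further specific questions. Whether that includes the primary pairwise contrasts is not stated.

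**The concern.** An ordinary ANCOVA estimates one error variance from all three arms and uses it for every pair. That is harmless if the arms vary equally, but here there are two reasons to expect otherwise. An arm that gains days at home moves toward a ceiling, where there is less room to vary. For CBI, the plan's own figures give the treated arm a smaller SD.

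Equal allocation makes a pooled two-arm t-test robust to unequal variances. It does not protect a contrast whose error variance is partly borrowed from a third arm. The comparisons at stake are the ones a three-arm design exists to make: whether case management alone helps (UP versus control), and whether the technology adds anything (UP-TECH versus UP).

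**Working it through.** **1. The plan's own figures.** The 150 per arm for days at home cannot be reproduced, because no mean or SD is given. It can be back-solved. With 150 × 0.85 = 127.5 analysed per arm, one-sided 5% and 80% power, the standardised difference is (1.645 + 0.842) × √(2/127.5) = 0.311. A 10% difference then implies an SD of about 0.10/0.311 = 32% of the mean. For CBI, with unequal SDs, n = (1.96 + 0.842)² × (18² + 12²)/8.5² gives 51 per arm, or 60 after 15% drop-out. So 150 per arm is ample, and the planned SDs do differ.

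**2. What the ceiling does.** Assume a 365-day ceiling. The largest possible SD at mean m is √(m(365 − m)). For a control mean of 310 (assumed) and a 10% gain to 341, it falls from √(310 × 55) = 130.6 to √(341 × 24) = 90.5 days. The SD implied by step 1 at a mean of 310 is 31/0.3115 = 99.5 days, which the treated arm could not have. At a control mean of 300 the limits are 139.6 and 107.5, so a common SD of 96.3 remains possible. The ceiling makes a smaller SD likely without fixing its size.

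**3. Days at home, only UP-TECH effective.** Let r = SD(UP-TECH)/SD(control), with UP the same as control and equal arm sizes.
- UP versus control: pooled SE/true SE is k = √((2 + r²)/3), and the actual two-sided error is 2 × (1 − Φ(1.96k)).
- UP-TECH versus UP (or control): pooled SE/true SE is √[((2 + r²)/3)/((1 + r²)/2)].

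| r | k | UP vs control, nominal 5% | Same at 0.05/3 | SE ratio, UP-TECH contrasts |
|---|---|---|---|---|
| 1 | 1.000 | 5.0% | 1.7% | 1.00 |
| 0.9 | 0.968 | 5.8% | 2.1% | 1.02 |
| 0.8 | 0.938 | 6.6% | 2.5% | 1.04 |
| 0.667 | 0.903 | 7.7% | 3.1% | 1.06 |
| 0.5 | 0.866 | 9.0% | 3.8% | 1.10 |

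One-sided at 5%, the error runs from 5.6% (r = 0.9) to 7.7% (r = 0.5).

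**4. Simulation, days at home.** Assumed: 127 per arm; 25% with short hospital stays; 10–25% institutionalised in control and UP, 5–10% in UP-TECH. SDs were 64–94 days against 46–64. In a covariate-adjusted model, UP-versus-control error was 7.0–8.0% with pooled variance and 4.5–5.2% with HC3. Power for UP-TECH versus UP rose by 3 to 7 points with HC3 (for example 56% to 63%); another simulation on similar assumptions gave 2 to 4 points. With all three arms identical, the pooled pairwise tests held 4.8–5.1%.

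**5. CBI, both interventions working (SDs 18/12/12).** Pooled variance = (324 + 144 + 144)/3 = 204, so a pairwise difference is given variance proportional to 408.
- Control versus UP: the true value is 324 + 144 = 468, and √(408/468) = 0.93. A nominal 95% interval misses 2 × (1 − Φ(1.96 × 0.934)) = 6.7% of the time.
- UP-TECH versus UP: the true value is 144 + 144 = 288, and √(408/288) = 1.19. A contrast with 80% power under the correct SE has Φ(2.80 − 1.96 × 1.19) = 68%.

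**The case against.** **The article does not fix the standard error.** ANCOVA with robust standard errors is still ANCOVA, and an analysis plan that is not shown may specify it. This is fair, and the point is limited to the ordinary form. It goes beyond missing detail because the named model, in its usual form, assumes equal variances and the sample size section of the same article plans unequal ones.

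**A reader might infer that UP versus control generally runs above 5%.** The documents do not support that. With no effect in any arm the test holds 5%. If UP works, that comparison has no type I error to inflate. Inflation needs UP ineffective and UP-TECH effective. Other contrasts err the opposite way: with both arms equally effective, simulated UP-versus-UP-TECH error for days at home was 2.5–3.0%.

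**A reader might take the 6.7% for CBI as a false-positive rate.** It is not. SDs of 18/12/12 go with a real treatment effect, so the figure is interval non-coverage.

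**The Bonferroni correction may cover this.** If it applies to the three primary contrasts, the error stays below 5% (2.1–3.8% for r from 0.9 to 0.5). That stands, but the stated scope is unclear, and the correction repairs neither the intervals nor the lost power.

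**The size for days at home is assumed.** It is. Observation time may also vary between patients. If deaths shorten it in 10–15% of patients equally across arms (a further assumption), r is 0.72–0.92 and the error about 5.3–7.4%.

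**Conclusion.** The point holds in conditional form. A pooled residual variance misstates pairwise standard errors whenever the arms differ in spread, which the plan itself expects for CBI and the ceiling makes likely for days at home.

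- **Days at home:** about 6% to 9% error for UP versus control, only if UP-TECH works, UP does not and no multiplicity correction applies. UP-TECH versus UP loses a few points of power. Both sizes depend on assumed SD ratios of roughly 0.9 to 0.5 or assumed event rates.
- **CBI:** the ratios 0.93 and 1.19 follow from the plan's own SDs, if both intervention arms have SD 12 and control has 18. They ignore covariate adjustment.

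The planned Kaplan-Meier and Cox analyses do not correct the ANCOVA contrasts. The change should be made before analysis, but the defect does not invalidate the design.

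**What to change.** Keep ANCOVA and the adjusted difference in means for both primary outcomes. State that pairwise tests and confidence intervals use HC3 standard errors, and say whether the Bonferroni correction covers the three primary contrasts.

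The cost is one option in the STATA model statement. If the variances turn out equal, the loss of precision is negligible at about 127 dyads per arm. Sample size, data collection and effect measure are unchanged.

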#### Multiple comparison issues

The issue of multiple comparisons will be carefully considered when investigating further specific questions. This issue will be addressed using two strategies. First, statistical adjustments for multiple comparisons will be used (for example the Bonferroni correction for analyses with less than 10 comparisons or the Tukey's test in the other cases, both available on STATA) to strengthen the criterion for judging a result as significant and reduce the likelihood of false-positive results. Second, future secondary and subgroup analyses will always indicate all the subgroups and outcomes considered in the trials. We will differentiate exploratory, sensitivity and other *post hoc* analyses from pre-specified analyses of the primary and secondary outcomes discussed in the protocol, and report them in any future publications.

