**Methods/design:**

A total of 450 dyads comprising AD patients and their caregivers in five health districts of the Marche region, Italy, will be randomized into three study arms. Participants in the first study arm will receive comprehensive care and support from a case manager (an *ad hoc* trained social worker) (UP group). Subjects in the second study arm will be similarly supported by a case manager, but in addition will receive a technological toolkit (UP-TECH group). Participants in the control arm will only receive brochures regarding available services. All subjects will be visited at home by a trained nurse who will assess them using a standardized questionnaire at enrollment (M0), 6 months (M6) and 12 months (M12). Follow-up telephone interviews are scheduled at 24 months (M24). The primary outcomes are: 1) caregiver burden, measured using the Caregiver Burden Inventory (CBI); and 2) the actual number of days spent at home during the study period, defined as the number of days free from institutionalizations, hospitalizations and stays in an observation unit of an emergency room.

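### Two primary outcomes each carry the full 0.05 with no rule for success, and the switch to Tukey at ten comparisons does not hold the error rate

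*Protocol article*

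**What the plan says.** The abstract and the outcomes section name two primary outcomes: CBI and "the actual number of days spent at home during the study period". Dyads "will be randomized into three study arms", in equal numbers: "In each block, five dyads will be allocated to each arm".

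Under Sample size calculation: "An estimation of the sample size was carried out by considering the two main outcomes separately". For CBI, "The statistical power was fixed at 80%, with a 0.05 significance level and a drop-out rate equal to 15" per cent. For days at home the type 1 error is again 0.05, in a one-tailed t-test of a 10% difference, also with 80% power and 15% drop-out. Neither paragraph divides the 0.05, ranks the outcomes or requires success on both.

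Under Statistics, each primary outcome is compared across the three groups by ANCOVA. No significance level and no arm contrasts are given there.

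Under Multiple comparison issues the opening sentence sets the scope: "The issue of multiple comparisons will be carefully considered when investigating further specific questions". The method is offered as an example: the "Bonferroni correction for analyses with less than 10 comparisons", and Tukey's test otherwise.

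**The concern.** Two separate things are at stake.

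1. **The primary family.** As written, a positive result on either outcome could be presented as a positive trial, and each is planned at 0.05. The adjustment text looks past the primary outcomes to later questions, so nothing stated limits the chance that at least one primary claim is false.

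2. **The rule itself.** Tukey's test controls error over all pairwise mean differences of one factor on one outcome. Three arms give three such pairs. In this trial a list of ten or more comparisons would normally come from several outcomes, visits or subgroups, where Tukey within each outcome does not control the total. Protection would be weakest where comparisons are most numerous.

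Power is linked to this. If the primaries are brought under control, the outcome planned with no margin (days at home) no longer has its stated 80%.

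**Working it through.** **Inputs.** From the sample-size section: 150 per arm, 15% drop-out (150 × 0.85 = 127.5, taken as 127 completers), 80% power, 0.05 per outcome; CBI 32.5 (SD 18) against 24 (SD 12), difference 8.5; days at home one-tailed, 10% difference, no mean or SD. Assumed, because the documents give no figure: correlation between the two outcomes from 0 to 0.8.

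**1. The plan's own figures.**

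- CBI: pooled SD = √((18² + 12²)/2) = 15.30. n = 2 × (1.960 + 0.842)² × 15.30² / 8.5² = 51 per arm two-sided, and 51/0.85 = 60 with drop-out. So 150 is more than sufficient (power 99.3% at 127 per arm) but is not the number that gives 80%.
- Days at home: this cannot be reproduced without an SD. Solving backwards from 127 completers, the standardised effect is (1.645 + 0.842) × √(2/127) = 0.312, which means an SD of about 0.10/0.312 = 32% of the mean.

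**2. Familywise error for the primary outcomes** (global null, three equal arms, 400,000 simulated trials, two-sided tests at 0.05):

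| What counts as a primary claim | Correlation 0 | 0.5 | 0.8 |
|---|---|---|---|
| Two three-group ANCOVA F tests | 9.7% | 9.1% | 7.9% |
| Four active-against-control contrasts | 17.3% | 16.1% | 14.0% |
| Six pairwise contrasts | 22.8% | 21.3% | 18.5% |

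For two independent tests the exact value is 1 − 0.95² = 9.75%, which agrees with the first row. With days at home one-tailed, the second row is 17.0%, 16.2% and 14.9%.

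**3. The adjustment rule.**

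- Bonferroni over four or six tests: 3.7% to 4.7%. Over nine independent tests: 1 − (1 − 0.05/9)⁹ = 4.9%. This part works.
- Tukey within each of two outcomes (six comparisons): 9.7% at correlation 0.
- Tukey within each of four outcomes (12 comparisons): 1 − 0.95⁴ = 18.5% if independent; 15.8% at correlation 0.5.
- Tukey within each of eight outcomes (24 comparisons): 1 − 0.95⁸ = 33.7% if independent; 25.5% at correlation 0.5.

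**4. Power once alpha is divided** (127 completers per arm). Power = Φ(effect/standard error − critical value). For days at home, effect/standard error = 0.312 × √(127/2) = 2.487.

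| Level per test | CBI, two-sided, SD 18/12 | CBI, two-sided, SD 18 in both arms | Days at home, one-tailed | Days at home: n per arm for 80%, with drop-out |
|---|---|---|---|---|
| 0.05 | 99.3% | 96.4% | 80.0% | 150 |
| 0.025 (two outcomes) | 98.6% | 93.6% | Φ(2.487 − 1.960) = 70.1% | 191 |
| 0.0125 (four contrasts) | 97.3% | 89.7% | 59.7% | 231 |
| 0.0083 (six contrasts) | 96.3% | 87.0% | 53.7% | 255 |

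**The case against.** The strongest reply is that the protocol specifies one three-group ANCOVA per primary outcome. That makes two tests, not four or six, and an error of at most 9.75%. This stands. A reader might infer that the plan as written carries an error of 16% or more, because the sample size is argued as treated against untreated and there are two treated arms. But no section names those contrasts as primary tests, so the larger figures are conditional.

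Four further readings go too far:

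- *The whole adjustment rule fails.* It does not. Bonferroni controls the error for any family it is applied to. For three pairwise contrasts Tukey is slightly sharper (about 0.019 per comparison against 0.05/3 = 0.0167), but that is a matter of efficiency.
- *Ten comparisons can never suit Tukey.* A five-level factor on one outcome gives 5 × 4/2 = 10 pairs, and there Tukey is valid. The trial has five health districts, though no comparison between them is planned. The rule is also only an example, but it is the only one given.
- *The sample-size and multiplicity sections contradict each other.* If the multiplicity text covers only later questions, it leaves the primary alpha alone and there is no conflict. The stated power is lost only once the primaries are adjusted.
- *Every visit is a primary test.* Days at home "will be calculated at each assessment (6 months, M6; 12 months, M12; and 24 months, M24"), but that says when the variable is computed. The sample-size section refers to the past year. Naming the primary visit can be left to the analysis plan.

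It can also be said that a condensed article leaves contrasts and procedures to an analysis plan that is not shown. That is fair for detail. It does not cover a scope sentence that looks past the primaries, or a stated rule that gives the wrong error rate.

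**Conclusion.** The point holds in this form. Two primary outcomes are each planned at the full 0.05 with no success rule, and the stated multiplicity control is tied to further questions. On the analysis as written, the chance of at least one false primary claim is about 8% to 10%, up to twice the nominal level. It would be 14% to 17% (four contrasts) or 18% to 23% (six) only if unadjusted arm contrasts were also treated as primary claims. If success required both outcomes no split would be needed, but the article does not say so.

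The Bonferroni part of the rule is sound and the Tukey switch is not: about 16% to 18.5% over 12 comparisons and 26% to 34% over 24, when these run across outcomes.

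These figures assume equal arms, the global null and a correlation between outcomes of 0 to 0.8 (0 to 0.5 for the Tukey cases). The 0.05 is taken from the sample-size text, because the Statistics section gives no level. The power loss for days at home, 80% to about 70%, rests on the back-solved effect of 0.31 SD and keeps the planned one-tailed test. A reader might instead quote a fall from about 70% to 60%. Those are the same effect tested two-sided at 0.05 and 0.025, so 60% mixes the alpha split with a change of sidedness.

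**What to change.** 1. State what counts as success. If either primary suffices, test each at 0.025 or use Holm. If both must succeed, say so and keep 0.05 for each.
2. Within each primary outcome, test the three-group ANCOVA F first and, if it is significant, the pairwise contrasts at the same level. For exactly three groups this is a closed procedure and needs no further penalty.
3. If Holm is used together with step 2, let the second outcome move up to 0.05 only after the F test and all contrasts of the first have been rejected at 0.025. Otherwise the two parts can add to 0.025 + 0.05 = 0.075. The fixed split at 0.025 avoids this.
4. Replace the count-of-ten rule by Tukey for pairwise contrasts within one outcome, and Holm or Bonferroni across outcomes.
5. Restate the power for days at home, with the mean and SD assumed.

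**Cost.** Wording, settled before any unblinded analysis, and some power. At 0.025 CBI keeps about 94% to 99% (two-sided). Days at home falls to about 70% one-tailed, and would need 191 per arm instead of 150 to regain 80%. The F test has no direction. If the contrasts after it are read two-sided at 0.025, power for days at home is at most about 60%. The further loss comes from giving up the one-tailed test, not from the split, so the restated calculation should say which test it assumes. If both outcomes must succeed, nothing is split, but the chance of success cannot exceed the 80% for days at home (about 0.993 × 0.80 = 79% if the outcomes are independent).
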